### Measurements

The outcome measurements will be assessed at three time points. Baseline measures will occur prior to randomisation of the depots into the two study arms. A second set of identical measurements will take place 6 months postrandomisation (ie, just after the completion of the 6-month intervention), and a final set will be taken at 12 months postrandomisation to assess the sustainability of the intervention (ie, 6 months after completion of the formal intervention period, as recommended by the National Obesity Observatory).^38^ At the baseline assessment, the study will be explained to the participant and written informed consent will be obtained. The measurements will be undertaken in suitable rooms within participating depots by trained researchers and will last between 1.5 and 2 hours per participant. Participants will complete a range of self-report questionnaires and have a series of physiological health assessments taken. All participants will receive detailed feedback on their physiological health assessment measures during each measurement session. In the event that a potential health issue is evident during the health assessments, such as undiagnosed hypertension or high cholesterol levels, participants will be advised to visit their GP for further checks. We will provide participants with a letter to give to their GP which summarises the findings from our point-of-care (blood markers) and automated (blood pressure) measures. Participants will be requested to inform the researchers about the use of any prescribed medications that they commence throughout the study duration which may impact the proposed outcome measures. Participants will be issued with objective monitoring devices to assess their free-living physical activity, sedentary behaviour and sleep, which they will be instructed to wear for 8 days following each measurement visit. After 8 days, participants will be requested to return these monitors to their depot where they will be collected by a member of the research team.

#### Primary outcome

The primary outcome will be physical activity, expressed as steps/day, at 12 months postrandomisation. Physical activity will be objectively measured using the activPAL microaccelerometer, worn continuously on the anterior aspect of the thigh, for 24 hours/day over 8 days during each assessment period. The activPAL provides a valid measure of walking and posture (ie, sitting and standing) in adults,^39–41^ and provides a more accurate measure of physical activity and sitting in occupational drivers in comparison to waist-worn accelerometers.^42^ As the physical activity component of the intervention predominantly includes the promotion of walking-based activity, and as participants will be provided with a Fitbit providing information on daily step counts to set goals to increase their physical activity, steps/day was chosen as the primary physical activity-related outcome.

#### Secondary outcomes

A number of secondary outcomes will be assessed at all measurement time points. The secondary outcomes are described as follows:

##### ​Physical activity and sedentary behaviour

Light physical activity and MVPA will be assessed using the activPAL and the wrist-worn GENEActiv accelerometer, both worn continuously for 8 days. The GENEActiv is a lightweight waterproof device, resembling a sports watch, which has been found to be a valid and reliable objective measure of physical activity.^43^ Outcomes calculated from the GENEActiv include minutes spent in MVPA, proportion of participants meeting the MVPA guidelines of 150 min/week, total volume of physical activity regardless of intensity, and sleep duration. The accelerometer provides time-stamped data so activity at specific times of the day (eg, during work, after work) will also be extracted.

Sedentary behaviour will also be measured for eight consecutive days during each assessment period using the activPAL3 micro. The activPAL is regarded as the most accurate method of assessing sitting behaviour in free-living settings,^41 44 45^ and is recommended for use in interventions when sitting is an outcome measure.^40^ From the data provided, we will extract total daily sitting time, work-time and leisure-time sitting, sitting bout durations and number of transitions between sitting and standing.

##### ​Sleep duration, subjective sleepiness and chronotype

Sleep duration and efficiency will be measured objectively using the GENEActiv which has been shown to be an accurate measure of sleep, in addition to physical activity.^46^ Subjective sleepiness will be assessed using the Karolinska Sleepiness Scale, shown to be a valid measure of sleepiness when validated against electroencephalography and performance outcomes.^47 48^ Participants’ chronotype will be determined using the short version of the Morningness-Eveningness Questionnaire.^49^

##### ​Anthropometry, adiposity and blood pressure

Stature (measured at baseline only) and body mass (both assessed without shoes), along with waist and hip circumferences, will be measured using standardised anthropometric techniques by trained research staff. BMI will be calculated as weight (kg)/height (m^2^). Body composition (percentage body fat and fat mass) will be assessed via bioimpedance analysis, using Tanita DC-360S body composition scales. We will also measure neck circumference which is a novel marker which links strongly to obstructive sleep apnoea, insulin resistance and cardiovascular disease risk.^50^ Blood pressure will be measured from the left arm after a 20 min period of quiet sitting using an automated recorder (Omron HEM-907), in accordance with current recommendations.^51^

##### ​Biochemical assessments

Finger-prick blood samples will be collected from participants, with participants being requested to fast for ≥4 hours prior to attending each health assessment. The ‘A1CNow^+^ point-of-care analyser will be used to measure HbA1c which is a marker of long-term glucose regulation used in clinical care. Additionally, we will use the Cardiochek point-of-care analyser to measure circulating cholesterol (total, HDL, LDL). Both of these systems are manufactured by PTS Diagnostics and possess analyte validation certificates from the International Federation of Clinical Chemistry and Laboratory Medicine.

##### ​Functional fitness

Grip strength will be assessed from both hands using the Takei Hand-Grip dynamometer (Takei Scientific Instruments, Japan). Reduced muscular strength, as measured by grip strength, is associated with an increased risk of cardiovascular disease, and all-cause and cardiovascular mortality.^52^

##### ​Cognitive function and psychophysiological reactivity

The Stroop test will be administered over a 5 min period using a validated software package to provide a measure of reaction time, sensitivity to interference and the ability to suppress an automated response—reading colour names in favour of naming the font colour.^53^ To examine psychophysiological reactivity, acute stress will be induced using a 5 min mirror-tracing task (Campden Instruments), during which measures of blood pressure and heart rate will be taken.^54^

##### ​Work-related psychosocial variables and mental health

A series of self-report measures will be employed to characterise work-related health and mental health: musculoskeletal symptoms will be assessed using the Standardised Nordic Questionnaire^55^; work engagement (characterised by vigour, dedication and absorption) will be measured using the Utrecht Work Engagement Scale^56^; occupational fatigue will be measured using the Occupational Fatigue Exhaustion Recovery 15 scale^57^; job performance^58^ and job satisfaction^59^ will be measured using single-item 7-point Likert scales; sickness presenteeism will be assessed using a single-item questionnaire; participant’s perceptions of work demand and support will be assessed using four subscales from the Health and Safety Executive Management Standards Indicator Tool,^60^ and driving-related safety behaviour will be assessed using a 6-item measure.^61^ Anxiety and depression will be measured using the Hospital Anxiety and Depression Scale,^62^ and social isolation will be assessed using the 8-item Social Isolation short form from the Patient-Reported Outcomes Measurement Information System.^63 64^ Data on sickness absence will be collected via self-report and employer records and will include frequency and duration of self-certified and certified sickness. Data on sickness absence will be collected from organisational records for 12 months prior to the intervention and for the 6-month intervention and follow-up periods.

##### ​Health-related quality of life and health-related resource use

The self-reported EQ5D^65^ will be completed by participants during each assessment period to inform the within-trial cost-effectiveness analysis (see ‘Cost-effectiveness’ section). Participants will also complete a questionnaire, developed for this study, assessing health-related resource use at the same time points.

##### ​Demographics and additional lifestyle health-related behaviour measures

At baseline we will collect basic demographic information for each participant including their date of birth, sex, ethnicity, highest level of education, marital status, postcode (to determine Index of Multiple Deprivation as an indicator of neighbourhood socioeconomic status), working hours, years worked as a HGV driver and years worked at our partner company. At each follow-up assessment, participants will be asked if there have been any changes in these variables. During each assessment, information on smoking status and typical alcohol intake will be gathered by self-report measures. Dietary quality, including fruit and vegetable intake, will be assessed using a short-form food frequency questionnaire.^66^

### Internal pilot

We intend to conduct an internal pilot study using the first six clusters (depots). The internal pilot will examine issues surrounding worksite and participant recruitment, randomisation, compliance to the primary outcome and retention rates at 6 months following randomisation. After this period, we will continue to the full trial if the following progression criteria are met:

All 24 depots required for the full sample size agree to take part in the study. Six depots will be selected to take part in the internal pilot (three will be randomised to the intervention arm and three to the control arm). This will demonstrate that depot recruitment and intervention delivery is on track.According to our criteria, 84 drivers will need to agree to participate in the internal pilot, based on an average of 14 participants per cluster.An average of 75% of drivers opting into the study, randomised into the intervention arm, attend the education session across the three intervention depots. This figure is based on the intervention uptake rate seen in our exploratory pre-post intervention study (87%),^20^ while also recognising that take-up rates tend to be lower when moving from an efficacy to a larger multicentre effectiveness trial.No more than 20% of participants fail to provide valid data for the primary outcome measure (activPAL-determined step counts) at baseline and at 6 months postrandomisation or withdraw/are lost to follow-up during the 6-month intervention phase. This threshold is necessary as study power requires total withdrawal or loss to follow-up of no higher than 30% during the 6-month intervention and 6-month follow-up (12 months postrandomisation).

If the final two progression criteria are not fully met, strategies to improve these metrics for the full trial will be discussed with the Trial Steering Committee and the study will progress based on recommendations from this committee.

### Process evaluation

The process evaluation will be used to help explain any discrepancies between expected and observed outcomes, to understand the influence of intervention components and context on the observed outcomes and to provide insight for any further intervention development and implementation.^22^ Throughout the intervention, we will monitor the reach, efficacy, adoption, implementation and maintenance of the intervention using the reach, efficacy, adoption, implementation, and maintenance (RE-AIM) framework.^67^ We will employ a variety of techniques (eg, logbooks, questionnaires, interviews and focus groups) to inform our process evaluation. For example, Transport Managers (or their nominated facilitators) and educators/worksite champions from each site will report on a monthly basis if there were any organisational changes (eg, job changes) or events which may affect participation. Self-report questionnaires provided to study participants will evaluate the various intervention components (eg, education session, physical activity monitoring tool, cab workout). Interviews and focus groups with study participants will further examine engagement in the various components of the intervention, along with any perceived barriers or facilitators to participating in these components. Interviews and focus groups with worksite champions, HR staff, health and safety personnel and logistics timetabling and planning staff will further examine the intervention implementation. We will also document any environmental factors (eg, movement of personnel between worksites/depots, potential contamination of the intervention through drivers in different groups meeting at service stations/customer distribution centres) that may have an influence on intervention effectiveness. Details of the process evaluation components are included in table 2.

**Table 2 T2:** Process evaluation plan for the SHIFT intervention

Areas to measure	General process questions	Data source and data collection method	Total numbers and sampling strategy/timescales
Recruitment	Number of depots/worksites invited to participate, and number agreeing. Number of possible participants at each depot, number invited/recommended for participation, number opting in to the intervention. Number of participants opting-out, dropping out and non-compliance to the primary outcome measure.	Project records, including the number of drivers within each depot approached. Depot logs of staff numbers, project records, attendance records at measurements. Participant attendance records, short questionnaires to explore reasons for non-participation, dropping out and non-compliance.	Ongoing throughout the project.
Acceptability of randomisation and measurement tools	How depots feel about being randomised to intervention/control arms? Did participants find outcome assessments acceptable? How did participants and logistics timetabling staff experience recruitment and timetabling of outcome assessments?	Focus groups with participants. Interviews with local depot health and safety advisors/HR/timetabling staff.	~8 focus groups, or until data saturation is reached, with participants ~1 month following completion of baseline measures. ~8 interviews, or until data saturation is reached, with local depot health and safety advisors/HR/timetabling staff ~1 month after completion of baseline measures in their depots.
Intervention acceptability and fidelity—implementation	Was the intervention implemented as planned? How did participants and logistics timetabling staff experience scheduling the education sessions?	Interviews with personnel within our logistics partners who are trained as educators and implemented the education sessions. Interviews with local worksite champions and timetabling staff within intervention depots. Participant questionnaires.	Interviews with educators, the number of which will depend on the number of educators trained, and timetabling staff immediately following delivery of the education sessions. Interviews with local champions 3 months into the intervention, immediately following the intervention (6 months), and at 9 and 12 months. Questionnaires administered after education sessions to participants.
Intervention acceptability and fidelity—participation	What proportion of the target group participated in the intervention, and what components of the intervention were preferred, did this differ between males and females? What strategies were put in place by intervention participants to facilitate behaviour change?	Focus groups with intervention participants. Attendance logs at education sessions and measurement visits. Questionnaires and focus groups.	~8 focus groups, or until data saturation is reached, with participants immediately following completion of the intervention (6 months). Brief questionnaires administered to all intervention participants at 6 months during health assessments.
Intervention sustainability	What proportion of the target group maintained any changes in their health behaviours following the 6-month intervention period? Were there any differences in sustainability between males and females? Are the company going to continue with the intervention in some way?	Focus groups with intervention participants. Questionnaires. Interviews with health and safety personnel.	~8 focus groups, or until data saturation is reached, with participants at 10 months follow-up (4 months after completion of the intervention). Brief questionnaires administered to all intervention participants at 12 months during health assessments. Interviews at 12 months.
Intervention contamination	Did movement of staff (eg, participants, health and safety personnel) occur from intervention to control depots? Did intervention drivers interact with control drivers at customer warehouses/distribution centres, etc?	Control depots to keep a log of any staff changes. Focus groups with intervention and control participants.	Logs collected on completion of the 12-month follow-up assessments. 8 focus groups, or until data saturation is reached, with intervention and control participants immediately following completion of the intervention (6 months) and at 10 months follow-up.
Unexpected events arising from the study	Did intervention and control participants modify their behaviours based on information provided at the baseline health assessments? Did the health assessments prompt general practitioner visits? Did increased self-awareness of health status and constraints within the job lead to cognitive dissonance? Did intervention participants change an existing activity-related behaviour for another as a result of participating in the study?	Focus groups, interviews and questionnaires delivered to intervention and control participants.	Questionnaires delivered to intervention and control participants 1 month after completion of the baseline health assessments. 8 focus groups, or until data saturation is reached, with intervention and control participants immediately following completion of the intervention (6 months) and at 10 months follow-up. One-to-one interviews based on questionnaire and focus group responses at 1 and 10 months.

### Patient and public involvement

This trial is the result of an earlier 3-year partnership between the research team and a large transport and logistics company (different to our partner in the present study) in the East Midlands, UK. The preparatory work which informed this study^3 7 16 17^ was instigated by the company who requested help in improving the lifestyle behaviours and health of their long-distance drivers who were proving difficult to engage. The SHIFT programme was developed in collaboration with long-distance HGV drivers and health and safety personnel working within the logistics sector. Following pilot testing, the intervention and outcome measures described within this protocol have been refined following further input from drivers and associated stakeholders. A driver and manager working within the logistics sector will sit on our independent Trial Steering Committee and will provide invaluable insight into the design, set-up, conduct and dissemination of this research. Throughout the trial, we will conduct regular patient and public involvement events with relevant stakeholders to gain feedback on the trial’s progress. The research team will also continue to work with the Chartered Institute of Logistics and Transport to facilitate research dissemination (articles, conferences, workshops) across the logistics and transport sector nationally and internationally.

### Data analysis

#### Statistical analysis: internal pilot

The average recruitment rate across depots, proportion of participants providing valid data and attendance rate at the education sessions will be reported with 95% CI. The point estimates and 95% CIs will be compared with the progression criteria outlined outlined in the Internal Pilot section

#### Statistical analysis: main trial

Average daily steps at 12 months will be compared by group using generalised estimating equation models adjusted for baseline values and waking wear time with an exchangeable correlation structure, which adjusts for clustering. For the primary analysis missing data will not be replaced (complete case analysis) but participants will be included in the intervention group in which their depots were randomised irrespective of the intervention actually received (modified intention-to-treat analysis). We have inflated our sample size by 30% to account for potential loss to follow-up and non-compliance with the primary outcome measure. We will compare the baseline characteristics of those who have complete primary outcome data and those who do not. A sensitivity analysis using multiple imputation will be performed to assess the impact of missing outcome data on the results found and to account for uncertainty associated with imputing data (full intention-to-treat analysis). The imputation will be carried out using the command MI in Stata. MI replaces missing values with multiple sets of simulated values to complete the data, performs standard analysis on each completed dataset and adjusts the obtained parameter estimates for missing data uncertainty using Rubin’s rules to combine estimates. The effect size will also be assessed by attendance excluding those who did not attend the full intervention (per-protocol analysis). Secondary outcomes and 6month data will be analysed using similar methodology.

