### Sample size

Our earlier exploratory pre-post study revealed that on average HGV drivers achieve 8786 steps/day across both workdays and non-workdays with a SD of 2919 steps.^20^ We have powered this study to look for a difference in step counts (the primary outcome) of 1500 steps/day (equivalent to approximately 15 min of moderately paced walking) between the intervention group and control group. Evidence demonstrates a linear association between step counts and a range of morbidity and mortality outcomes, as well as with markers of health status including inflammation and adiposity, insulin sensitivity and HDL-C in adults.^24–26^ The linear association between step counts and health outcomes indicate that regardless of an individual’s baseline value, even modest increases in daily step counts can yield clinically meaningful health benefits. For example, a difference in daily steps of 1500 steps/day has been associated with around a 5%–10% lower risk of all-cause mortality and cardiovascular morbidity and mortality in the general population and in those with a high risk of type two diabetes, respectively.^27 28^ The proposed level of change has been chosen based on findings from our exploratory pre-post intervention,^20^ while also being clinically meaningful.

Based on a cluster size of 10, a conservative ICC of 0.05 (as there is no previous data to inform this, we have been informed by recommendations of Campbell *et al*^29^), an alpha of 0.05, power of 80% and a coefficient of variation to allow for variation in cluster size of 0.51 (based on partner company data), we will require 110 participants from 11 clusters per arm. From experience in conducting such studies, it is estimated that retention and compliance rates will be approximately 70% at 12 months follow-up; therefore, the sample size will be inflated by 30% to ensure we have adequate power in our final analysis. We will also inflate the number of clusters by two to allow for whole cluster drop out. We will therefore recruit 24 clusters with an average of 14 participants per cluster.

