### Allocation to treatment groups

Clusters (depots within the same company) will be randomised at the worksite level into the two study arms (intervention and control, using an allocation ratio of 1:1). Randomisation into the study arms will take place in two batches; initially the first six clusters (depots) involved in the internal pilot (see below) will be randomised, and in the second batch all of the remaining clusters will be randomised stratified by depot size. Depots will be classified as either small or large based on the median cluster size of all participating depots. In both batches randomisation will take place on completion of baseline measurements and will be done by an independent statistician at the Leicester Clinical Trials Unit.

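### The complete-case rule in a baseline-adjusted primary model drops drivers with an observed 12-month step count but no valid baseline; this is a modest and avoidable departure from intention to treat, not a source of bias

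*Protocol article*

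**What the plan says.** Under *Statistical analysis: main trial*, the protocol fits a GEE to average daily steps at 12 months, adjusted for baseline values and waking wear time, with an exchangeable correlation structure. On missing data it states: "For the primary analysis missing data will not be replaced (complete case analysis"). No exception is made for the baseline covariate. Drivers are analysed in the arm of their depot, and the result is called modified intention to treat. A multiple-imputation sensitivity analysis follows, labelled full intention to treat and aimed at missing outcome data. Secondary outcomes and 6-month data are to be handled in a similar way.

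Invalid baseline monitor data are foreseen. One progression criterion under *Internal pilot* counts participants who "fail to provide valid data for the primary outcome measure (activPAL-determined step counts) at baseline and at 6 months postrandomisation". The *Measurements* section places baseline before randomisation. Valid baseline steps are not among the conditions listed under *Participant recruitment and exclusion criteria*.

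**The concern.** A GEE with baseline steps as a covariate cannot use a record in which that covariate is missing. If nothing is replaced, a driver whose baseline activPAL week failed leaves the primary analysis even though the primary outcome was measured.

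The monitor is worn for 8 days after the visit and then returned to the depot, so some baseline weeks may be lost among drivers who go on to give a valid 12-month week. Because baseline is taken before randomisation, allocation cannot cause a baseline to be missing, and these drivers can be kept without biasing the arm comparison. At stake are observed primary outcomes and the completeness of the analysed set. The same loss would recur in every baseline-adjusted secondary and 6-month analysis.

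**Working it through.** **Inputs from the *Sample size* and *Allocation to treatment groups* sections.** Target: "difference in step counts (the primary outcome) of 1500 steps/day". Mean and SD: "8786 steps/day across both workdays and non-workdays with a SD of 2919 steps". "Based on a cluster size of 10, a conservative ICC of 0.05". "a coefficient of variation to allow for variation in cluster size of 0.51". Error rates: "an alpha of 0.05, power of 80" per cent (two-sided assumed). Depots are randomised "using an allocation ratio of 1:1".

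**Reproducing the planned size.**
- Individually randomised: n = 2 × (1.960 + 0.842)² × 2919² / 1500² = 59.4 per arm.
- Design effect: 1 + ((1 + 0.51²) × 10 − 1) × 0.05 = 1.580.
- 59.4 × 1.580 = 93.9 per arm, or 9.4 clusters, rounded up to 10. One more cluster for the small number of clusters gives 11, that is 110 per arm.
- Check with a noncentral t on 2(k − 1) degrees of freedom: 78.1% power with 10 clusters per arm, 82.2% with 11.

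The stated 110 participants from 11 clusters per arm is reproduced. The calculation takes no credit for baseline adjustment.

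**Assumptions, not in the protocol.** A share q = 5%, 10% or 20% of 12-month completers lack a valid baseline. The baseline/12-month correlation ρ is 0.3 to 0.8.

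**Drivers lost.** Of 220 planned evaluable drivers: 11, 22 or 44.

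**Closed-form power, 11 clusters per arm.** Complete case uses mean cluster size 10(1 − q) and variance 2919²(1 − ρ²). Keeping everyone uses cluster size 10 and variance 2919²(1 − ρ²(1 − q)). Each cell shows complete case / keep all.

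| ρ | q = 5% | q = 10% | q = 20% |
|---|---|---|---|
| 0.3 | 84.5 / 85.4% | 83.3 / 85.3% | 80.5 / 84.9% |
| 0.5 | 90.6 / 91.0% | 89.7 / 90.6% | 87.4 / 89.7% |
| 0.7 | 97.8 / 97.6% | 97.4 / 97.1% | 96.4 / 95.9% |

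**Simulation of precision.** 22 clusters, mean size 10, CV 0.51, ICC 0.05, true effect 1500, exchangeable weighting with the working correlation fixed at 0.05, 12,000 trials per cell. Keep all uses mean imputation plus an indicator. Each cell is the complete-case SE divided by the keep-all SE.

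| ρ | q = 5% | q = 10% | q = 20% |
|---|---|---|---|
| 0.3 | 1.016 | 1.037 | 1.068 |
| 0.5 | 1.010 | 1.021 | 1.054 |
| 0.7 | 1.003 | 1.002 | 1.004 |
| 0.8 | 0.986 | 0.978 | 0.956 |

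Smaller runs of 3,000 trials gave ratios of 1.01 to 1.03 at 5-10% missing, and 1.07 to 1.09 at 20%, for ρ of 0.3 to 0.5. Differences of a percentage point or two between runs are simulation error.

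**Bias.** In the 3,000-trial runs the mean estimates were 1479 to 1514 against 1500, including scenarios where low baseline values were more likely to be missing. The two estimators never differed by more than 4 steps in any scenario. Neither is biased.

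**The case against.** The strongest reply is that this is a minor choice between two unbiased estimators. Most of it stands.

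- **Left to the SAP.** The paragraph never mentions a missing baseline, and its neighbouring sentences concern the outcome. Handling of covariates is often a SAP matter. Here, though, the protocol fixes a rule of no replacement without exception, and a SAP that filled in baselines would depart from it.
- **Disclosed and partly covered.** The analysis is openly called modified, and the multiple-imputation analysis is labelled full intention to treat. If that label is meant literally, these drivers return there. That is a fair point, but the primary result would still omit them.
- **Already in the 30% allowance.** A reader might infer that baseline failures come on top of the roughly 235 expected completers (24 × 14 × 0.70), removing about 12 at 5% or 24 at 10%. The documents do not settle this. The 70% covers retention and compliance, and the pilot criterion puts baseline failure, 6-month failure and withdrawal under one ceiling. Even if the losses are additional, 5% leaves about 223, above the required 220.
- **Comparison with whole depots.** A reader might equate 24 lost drivers with more than two depots of 10. Scattered losses cost less. With mean cluster size falling from 9.79 to 8.79, information per cluster, m / (1 + ((1 + CV²)m − 1) × ICC), falls from 6.25 to 5.85. That is about 6.5%, against 10% for losing 2.4 of 24 depots.
- **Not always less precise.** It is tempting to say that complete case never has a benefit. At ρ near 0.7 there is nothing to choose, and at 0.8 complete case is slightly more precise.

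**Conclusion.** The exclusion follows from the protocol's own wording and is worth correcting, but it is small. It discards observed primary outcomes and makes the primary analysis less complete than it could be.

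A reader might infer that the treatment estimate is biased or that the trial is underpowered. Neither is supported. Both approaches were unbiased, and complete-case power stays at or above 80.5% across ρ of 0.3 to 0.7 with up to 20% missing, because the planned 80% ignores the gain from baseline adjustment.

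The precision cost of complete case rests wholly on two assumed quantities. For ρ of 0.3 to 0.5 it is about 1-3% in the standard error at 5-10% missing and about 6-7% at 20%. In power this is at most about 4 points (80.5% against 84.9%, at ρ = 0.3 and 20% missing). Near ρ = 0.7 there is no gain from keeping everyone. At 0.8 there is a loss of about 1-3% at 5-10% missing, and somewhat more at 20%. The main benefit of the change is therefore a fuller intention-to-treat set, with precision a secondary and conditional gain.

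**What to change.** Amend the missing-data sentence in *Statistical analysis: main trial* along these lines: the primary analysis includes every randomised driver with a valid 12-month step count, in the arm of their depot; a missing baseline step count is set to the overall baseline mean across both arms, and a missing-baseline indicator is added to the model; missing 12-month outcomes are not replaced; the strict complete-case set is reported as a sensitivity analysis. State that the same rule applies to the baseline covariate in the secondary and 6-month analyses, and say whether the multiple-imputation analysis also imputes missing baselines.

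The cost is a sentence or two, with no new data and no change in sample size. The possible price is the small loss of precision if baseline and 12-month steps are very highly correlated. The change should be made before outcome data are seen by arm, so that the analysed set is not chosen afterwards.
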